### 2.9. Sample Size

The mean annual CAC-progression reported in literature ranges from 24% to 51% and has a large inter-individual variation depending on many factors such as the baseline CAC-score, medical history, medication-use, body-mass index, scanner type and manufacturer. The standard deviation in CAC-score progression in a population comparable to our intended population is reported to range from 21% to 36% [33]. Since we use strict inclusion and exclusion criteria and use a 128-slice MDCT with better reproducibility of measurements, we estimate the standard deviation of CAC-progression to be 25%. We consider an absolute difference of 15% in CAC-progression between the two treatment groups a significant effect [33]. To test this difference with a statistical power of 90% (alpha 0.05) we require 59 patients per group. Based on analysis of available data from our center, we estimate a patient drop-out of approximately 35%. This drop-out may have various reasons such as patients requiring coronary artery stenting over the course of the study, occurrence of cardiovascular events such as myocardial infarction requiring percutaneous coronary intervention (PCI) or death, development of exclusion criteria, or subjects no longer willing to participate in the study. Therefore, to obtain sufficient statistical power to demonstrate a possible treatment-effect, we require 90 patients per group for a total number of 180 patients.

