### 2.5. Treatment Schedule

Treatment of both groups will last for 24 months. During this time participants will visit our research unit five times, at 6-month intervals (Figure 1). At every study visit we will perform an interview and blood pressure measurements. During the first visit, at 12, and at 24 months of follow-up, measurements of CABP, cfPWV, crPWV, cIMT and DC are scheduled. In addition, fasting blood-samples will be drawn at 0, 12, and 24 months. We will repeat CT-scans of the heart and coronary arteries at 12 and 24 months of follow-up. At 12 months only a non-contrast CT scan will be performed to obtain a calcium score. At 24 months a CT-angiography will be performed, using the same acquisition protocol and reconstruction techniques as the initial CT scan (See Figure 1).

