### 2.8. Statistical Analysis

The main outcome parameters (CAC-score) and CAC-score progression will be presented as continuous variables. In addition, the amount of CAC-score progression (in both Agatston-score and Mass-score) will be dichotomized (rapid progression and slow progression) using a cut-off of an annual progression of 15% [33].

Data will be analyzed based on the intention-to-treat principle. To adjust for potential confounders (age, gender, BMI, blood-pressure, smoking, cholesterol, glucose and medication use), multiple analysis of variance will be performed. For continuous variables, multivariable linear regression will be applied. For longitudinal data analysis (*i.e.*, progression between baseline, 12 months, and 24 months of follow-up) Generalized Estimating Equations (GEE) analysis will be applied to adjust for multiple testing. Additional statistical analyses will be performed as appropriate (e.g., Hazzard ratio calculation). All statistical analysis will be performed using the statistical package SPSS 22 (IBM Corp, Armonk, New York, USA). The statistical tests will be performed using a two-sided significance level of 5%.

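### With about 35% drop-out expected, partly from cardiac events, GEE is a fragile choice for the longitudinal CAC analysis; a likelihood mixed model using the 12-month scan is safer at little cost

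*Protocol article*

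**What the plan says.** All places are in the protocol article.

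- **Section 2.9 (Sample Size).** The effect is fixed thus: "We consider an absolute difference of 15% in CAC-progression between the two treatment groups a significant effect". For the spread, "we estimate the standard deviation of CAC-progression to be 25" (percent). Then "To test this difference with a statistical power of 90% (alpha 0.05) we require 59 patients per group". Total drop-out is put at about 35% from the centre's own data, with these causes first: "This drop-out may have various reasons such as patients requiring coronary artery stenting over the course of the study, occurrence of cardiovascular events". New exclusion criteria and unwillingness to continue follow. No share is given for any cause, nor any timing or split by arm. The result is "we require 90 patients per group for a total number of 180 patients".
- **Section 2.8 (Statistical Analysis).** Under intention-to-treat, "Generalized Estimating Equations (GEE) analysis will be applied" to the data at baseline, 12 and 24 months. The reason given is multiplicity; drop-out is not mentioned. Working correlation and weighting are not stated. Multiple analysis of variance and linear regression are named alongside.
- **Section 2.5 (Treatment Schedule).** "We will repeat CT-scans of the heart and coronary arteries at 12 and 24 months of follow-up". A patient lost after month 12 therefore already has an interim calcium score.
- **Section 2.10.5** adds withdrawal for poor adherence and for starting a vitamin K antagonist.

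**The concern.** The method named for the longitudinal outcome and the loss the protocol expects do not fit well together. Without weighting, GEE gives consistent estimates in general only if the chance of a missing scan is unrelated to the outcomes, given the model covariates.

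The protocol's own reasoning makes that doubtful for part of the loss. Section 1 treats CAC as a strong risk marker for cardiovascular complications and its yearly change as a reflection of plaque burden. Patients who progress fast by month 12 are then plausibly more likely to need a stent, have an infarction or die, and so to have no 24-month scan. If placebo patients progress faster, more of the fast progressors leave that arm, and the arms look more alike than they are.

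Raising the sample from 59 to 90 per group protects power, not the estimate. With about one patient in three expected to be lost, the missing-data assumption behind the chosen method bears directly on the 24-month comparison.

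**Working it through.** **1. The plan's own figures.** Inputs from section 2.9: difference 15, SD 25, power 90%, alpha 0.05 (two-sided in section 2.8).

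- n = 2 × (1.960 + 1.282)² × 25² / 15² = 58.4, so 59 per group, as stated.
- 59 / 0.65 = 90.8, so 91 against the stated 90, a trivial difference. 90 × 0.65 = 58.5 completers per group give 90.1% power.

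The sample size is not in dispute.

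**2. Where the bias comes from.** Let Y1 and Y2 be progression at 12 and 24 months, both with SD 25, correlation ρ and a true difference of 15. Let loss after month 12 follow a logistic model in Y1, with log-odds s per SD. With an independence working correlation the 24-month contrast is the completers' contrast:

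estimate = 15 + ρ × (d_placebo − d_MK-7),

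where d is the completers' mean Y1 minus the mean Y1 of everyone in that arm. Only 35%, 25 and 15 come from the protocol; ρ, s and the timing of loss are assumptions.

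For s = 2, numerical integration with the intercept set to 35% overall loss gives d = −13.16 (placebo) and −8.44 (MK-7). Loss is then 43% against 27%. With ρ = 0.7 the estimate is 15 + 0.7 × (−4.72) = 11.7. For s = 1, d = −8.44 and −6.19, giving 15 + 0.7 × (−2.25) = 13.4. For s = 0.25, d = −2.26 and −2.05, giving 15 + 0.7 × (−0.21) = 14.9.

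**3. Simulation.** 300,000 patients per arm; ρ of 0.5 or 0.7; s of 1 or 2; none, half or all of the loss before month 12. Monte Carlo error is about 25 × √(2/195,000) = 0.08. The truth is 15 in every row except the last.

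| Loss mechanism | GEE, independence | GEE, exchangeable | Mixed model |
|---|---|---|---|
| Completely at random | 14.9–15.1 | 14.9–15.1 | 14.9–15.1 |
| Depends on 12-month score, both arms | 11.7–14.1 | 14.6–14.9 | 14.9–15.2 |
| Depends on 12-month score, MK-7 arm only | 17.1–20.0 | 14.9–15.3 | 14.9–15.1 |
| Depends on the unseen score, some or all loss after month 12 | 10.2–12.7 | 10.9–13.7 | 10.9–13.7 |
| Outcome-related, all loss before month 12 | 11.6–13.8 | 11.6–13.8 | 11.6–13.8 |
| No true effect, same mechanism in both arms | within 0.05 of 0 | within 0.05 of 0 | within 0.05 of 0 |

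In some settings of the fourth row total loss came out at 31% to 34%.

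**4. Size.** In row two, independence GEE attenuates by (15 − 14.1)/15 = 6% to (15 − 11.7)/15 = 22%. With the weak dependence of step 2 it is (15 − 14.9)/15, about 1%. Exchangeable GEE attenuates by at most (15 − 14.6)/15, about 3%. In row three independence GEE exaggerates by (17.1 − 15)/15 = 14% to (20.0 − 15)/15 = 33%.

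The standard error with 58.5 completers per arm is 25 × √(2/58.5) = 4.62. Holding it fixed, an expected estimate of 13.4 corresponds to power Φ(13.4/4.62 − 1.96), about 83%. An estimate of 11.7 corresponds to about 72%. The plan has 90%.

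**5. A second set-up.** 2,000 trials of 90 per arm; random slopes SD 18, residual SD 17; true 24-month difference −30; 35% lost, all after month 12.

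| Odds of loss per 10 points of 12-month progression | GEE, independence | GEE, exchangeable | Likelihood |
|---|---|---|---|
| 1.65-fold | −26.8 | −28.8 | −29.9 |
| 2.2-fold | −25.1 | −28.1 | −30.1 |

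With a milder log-odds of 0.03 per point, independence gives −28.5 and exchangeable −29.5. With no dependence both approaches are unbiased and likelihood has the smaller standard error (6.95 against 7.46).

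**The case against.** A reader might infer that the whole 35% comes from progression-related events. The text does not say that. It is total loss with mixed causes, and some of them (unwillingness, poor adherence, starting a vitamin K antagonist) have no evident tie to calcium progression.

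A reader might also infer that a mixed model would correct the bias outright. It does so only if loss is at random given the observed scores. A stent or infarction may reflect disease since the last scan, and anyone lost before month 12 has no interim score. In those cases the mixed model is biased too, as the table shows.

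Further points stand:

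- The larger attenuations belong to an independence working correlation, which the article does not specify. A common exchangeable structure removes most of the bias when loss follows the 12-month score.
- The assumed dependence is strong. Log-odds of 1 and 2 per SD mean odds of loss rising 2.7-fold and 7.4-fold per SD, with loss differing between arms by 11 to 17 points in the both-arms scenario when all loss follows month 12. Nothing in the document supports such values.
- With no true effect and the same mechanism in both arms there is no bias. With a true effect the error is then conservative. Exaggeration needs a mechanism that differs by arm.
- Working correlation, weighting and missing-data rules may be set out in a fuller protocol or analysis plan that is not shown. Their absence from an article is no fault.

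What this leaves untouched is that the article does choose a method. It chooses GEE for a reason unrelated to drop-out, and the 12-month score that a likelihood model could use is already scheduled.

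**Conclusion.** The point holds as a recommendation about a stated method. The protocol names GEE, expects about 35% loss, and lists cardiac events that its own rationale links to CAC progression among the causes. Unless GEE is weighted, the 24-month effect can be biased.

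If loss depends on the 12-month score in the same way in both arms, the attenuation is roughly 1% to 20% with an independence working correlation and a few percent with an exchangeable one. If the mechanism operates in the MK-7 arm only, the error goes the other way. These sizes rest on assumed correlation, strength of dependence and timing of loss, none of which the document gives.

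The document does not support saying that the result will be wrong, or by how much.

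**What to change.** - **Main longitudinal analysis.** Replace GEE by a linear mixed model for repeated measures, fitted by REML to (log) CAC at 12 and 24 months. Use an unstructured covariance, treatment-by-visit terms, baseline CAC and the minimisation factors of section 2.7 (age, sex, BMI, statin and bisphosphonate use). Name the 24-month contrast as the test. This is valid under missing at random and uses the interim scan of patients lost later.
- **One sensitivity analysis.** Add a delta-shift analysis for patients lost to PCI, infarction or death, and for those lost before month 12, over a stated range of shifts. These are the groups the mixed model cannot fully protect.

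Cost: revised analysis wording and a few days of programming, with no change to sample size, visits or scans. The main downside is reliance on a normal model for the (log) score. A log-scale contrast is also a ratio, so the write-up must relate it to the 15-point difference used for the sample size.

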### 2.10. Organization

#### 2.10.1. Data Safety Monitoring Board (DSMB)

An independent DSMB will be established to perform ongoing safety surveillance and to perform interim analyses on the safety data. None of the DSMB-members are directly or indirectly involved in the coordination, execution or analysis of the proposed study.

The DSMB’s primary task is to monitor the safety of participants. Interim analysis will be performed to assess whether a treatment-group has relatively more adverse events than the other. The DSMB will assess the number of cardiovascular events (myocardial infarction, coronary revascularization procedures, and cardiovascular deaths) and the number of adverse reactions/side effects as reported by the study-participants at every interim analysis.

Furthermore, the DSMB will calculate the rate of progression of vascular calcification in both groups. If there is a reason for concern, the DSMB can advise to interrupt the study for further analysis or terminate the study. This will be discussed in a meeting with the investigators and DSMB.

The investigator will inform the subjects and the reviewing accredited MEC if anything occurs, on the basis of which it appears that the disadvantages of participation may be significantly greater than was foreseen in the research proposal.

#### 2.10.2. Adverse and Serious Adverse Events (AE and SAE)

Adverse events are defined as any undesirable experience occurring to a subject during a clinical trial, whether or not they are considered related to the investigational drug. All adverse events are recorded. An abnormal laboratory result will not be considered as an adverse event except where it is indicative of disease and/or organ toxicity. Details of all adverse events reported spontaneously by subjects or observed by the investigator or medical staff will be recorded. All SAEs will be reported to the accredited MEC that approved the protocol, according to the local requirements.

#### 2.10.3. Suspected Unexpected Serious Adverse Reactions (SUSAR)

Adverse reactions are all untoward and unintended responses to an investigational product related to any dose administered. Unexpected adverse reactions are adverse reactions, of a nature or severity that is not consistent with the applicable product information. The investigator will report all SUSARs to the MEC. In case of a SUSAR, the randomization-code will be broken for the individual patient only so blinding of treatment allocation can be maintained for the remaining study subjects. The treatment allocation of that individual patient will be reported to the investigators.

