### 2.2. Patient Recruitment

The VitaK-CAC trial is a double-blind, randomized, placebo-controlled trial in two centers. Eligible patients suspected of having coronary artery disease (CAD) and who are scanned by 128-slice multiple detector CT (MDCT) to assess the presence of coronary atherosclerotic plaques and CAC will be identified from the outpatient clinic of the departments of Cardiology. Patients with a baseline Agatston CAC-score between 50 and 400 will be recruited and randomized into two groups. This Agatston score corresponds with a moderately increased risk of cardiovascular events or death [2].

The study has been approved by the Medical Ethics Committee (MEC) of the Maastricht University Medical Center, Maastricht, the Netherlands. The study complies with the Declaration of Helsinki. All patients have to give written informed consent.

The VitaK-CAC trial is registered at clinicaltrials.gov as NCT01002157.

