### 2.6. Vitamin K Product

Subjects in the intervention group will receive a once-daily oral tablet of 360 micrograms of MK-7. In our study we use a pure synthetic MK-7 provided by NattoPharma ASA (Hovik, Norway). The choice for MK-7 as K-vitamer is based on the longer half-life and extra-hepatic tissue distribution as compared to other vitamin K-forms [12,24]. The chosen dose in this trial was established in a dose-finding study, in which the effect of increasing doses of MK-7 on OCN and MGP-carboxylation was monitored. A daily dose of 360 μg MK-7 most effectively reduced the amount of non-functional MGP [22,32].

MK-7 is well tolerated and does not cause a hypercoagulable state [33]. There are no reported adverse effects associated with the use of MK-7.

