### 2.7. Randomization Procedure

If the patient is eligible and willing to participate in the study, the patient will be randomly assigned to the MK-7 or placebo group. Subjects will be randomized after stratification for age, sex, BMI, statin- and bisphosphonate-use using the minimization technique [34]. An independent investigator who is not involved in the coordination or analysis of this study, will randomize consecutive patients using custom-made computer software. The randomization-list will be stored in a secure location and will not be accessible to the investigators during the study.

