#### 2.10.5. Withdrawal of Individual Subjects

Subjects can leave the study at any time for any reason if they wish to do so, without any consequences. The investigator can decide to withdraw a subject from the study for urgent medical reasons or in case of demonstrable poor adherence to the study medication. This is assessed by interview and pill-count. If subjects are required to take vitamin-K antagonists (coumarins) during the course of the study (for example due to Deep-Venous Thrombosis or Pulmonary Embolism) they will be withdrawn from the study.

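### After every SUSAR the patient's allocation goes to the investigators with no need-to-know limit, which needlessly weakens the double-blind for later judgements

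*Protocol article*

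**What the plan says.** Section 2.2 describes the design: "The VitaK-CAC trial is a double-blind, randomized, placebo-controlled trial in two centers". Section 2.7 gives the randomization to an independent person outside the coordination and analysis of the study, and adds: "The randomization-list will be stored in a secure location and will not be accessible to the investigators during the study".

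Section 2.10.3 sets the procedure after a SUSAR. On reporting: "The investigator will report all SUSARs to the MEC". On the code break: "the randomization-code will be broken for the individual patient only so blinding of treatment allocation can be maintained for the remaining study subjects". On who is told: "The treatment allocation of that individual patient will be reported to the investigators". The section does not say who breaks the code, what the disclosure is for, or which investigators receive it.

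Two other places bear on the point. Section 2.10.5 leaves withdrawal partly to judgement: "The investigator can decide to withdraw a subject from the study for urgent medical reasons", with demonstrable poor adherence as the other ground. Section 2.6 says of the product: "There are no reported adverse effects associated with the use of MK-7".

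**The concern.** The code break is kept narrow to protect the blind, but its result then goes to the group whose judgements the blind is there to protect. Investigators go on seeing patients at six-month intervals, recording adverse events and adherence, and deciding on withdrawal. Once told, they make those judgements about the SUSAR patient in the knowledge of the arm. If they learn that a certain kind of reaction occurred on MK-7, or on placebo, they may also look differently at the next similar event in a patient who is still blinded. Breaking the code for one patient only does not prevent that carry-over.

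At stake is mainly the quality of safety and withdrawal judgements. The primary comparison is touched only through the few patients concerned.

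**Working it through.** **1. The sections side by side**

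| Section | What it fixes | Bearing on the point |
|---|---|---|
| 2.2 | Double-blind trial, two centers | Investigators are meant not to know allocation |
| 2.7 | List closed to investigators; independent person randomizes | Protects the list; silent on disclosing a single allocation |
| 2.10.3 | One code broken per SUSAR; result goes to the investigators | Express single-patient exception with no need-to-know limit |
| 2.10.2 | Investigator or staff observe and record adverse events | A judgement exposed after disclosure |
| 2.10.5 | Investigator may withdraw a subject on two grounds | A judgement exposed after disclosure |
| 2.4.2 | A cardiologist and a radiologist read the scans | Not stated whether they are among those told |

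Sections 2.7 and 2.10.3 can both be obeyed: the list stays closed while one allocation is released. So there is no contradiction. What remains is a release wider than any purpose the article states.

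**2. Order of events.** An event must be judged related before it can be a SUSAR, and the code is broken afterwards. The judgement that triggers the disclosure is therefore still blinded. Only later judgements are exposed.

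**3. How often.** Section 2.6 reports no adverse effects of MK-7, so almost any serious event judged related would count as unexpected. That makes expectedness a weak filter, but it also suggests that few related events will occur. No expected number is given. As an assumption, take 1 to 5:

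- 1/180 = 0.6% of patients
- 5/180 = 2.8% of patients

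**4. Scale on the primary comparison.** Inputs from Sections 2.8 and 2.9: difference 15 points, SD 25 points, two-sided 5%, power 90%, 59 per group.

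The plan's own figure reproduces: n = 2 × (1.96 + 1.2816)² × (25/15)² = 58.4, rounded up to 59. With 59 per group the standard error is 25 × √(2/59) = 4.60, and power is Φ(15/4.60 − 1.96) = 90.3%.

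Now suppose that k unblinded patients all fall in one arm of 59 and that knowledge of the arm distorts each one's result by b points towards no difference. The group difference shifts by k × b/59. Both k and b are assumptions; the article gives neither.

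| k | b | Shift (points) | Share of 15 | Power |
|---|---|---|---|---|
| 1 | 5 | 0.08 | 0.6% | 90.0% |
| 1 | 25 | 0.42 | 2.8% | 88.6% |
| 5 | 5 | 0.42 | 2.8% | 88.6% |
| 5 | 25 | 2.12 | 14.1% | 79.9% |

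The last row is a deliberate extreme: five SUSARs, all in one arm, each distorted by a full SD, and all in the same direction. It also supposes that the distortion reaches the CT score, which the article gives no ground to assume.

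**The case against.** The strongest case against has five parts.

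- **No rule is broken.** A reader might infer that Section 2.10.3 violates a ban on investigators knowing any allocation. Section 2.7 contains no such ban. It says that the list "will not be accessible to the investigators during the study", and Section 2.10.3 is a compatible exception. This stands.
- **CT reading is not shown to be affected.** A reader might infer biased calcium scores. The article does not place the two readers among those told, though it does not exclude them either. This stands.
- **The safety board and the stopping clause are not shown to depend on unblinded investigators.** Section 2.10.1 counts reactions reported by participants, together with cardiovascular events. Section 2.10.4 uses the number of serious adverse events, and its causality clause names no judge. This stands, so bias in the board's counts or in a termination decision cannot be claimed.
- **Carry-over need not differ by arm.** Other patients remain blinded, so a changed threshold for relatedness or withdrawal applies to both arms alike. The withdrawal grounds are limited, adherence is checked by pill-count, and analysis is by intention to treat. This largely stands: carry-over threatens the consistency of judgements and is not evidence of a biased comparison. It does not answer the loss of blinding for the SUSAR patient.
- **A condensed article leaves such detail to the full protocol.** This holds for logging and for arrangements to shield readers. It does not dispose of the point, because the article states a positive rule on who is told, and following it as written unblinds the investigators.

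It is also true that the article gives no purpose for the code break, and that requirements not shown may govern what the report to the ethics committee must contain. The fix allows for this by sending the allocation to the committee.

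**Conclusion.** The point holds as a minor weakness in blinding. As written, every SUSAR reveals that patient's arm to the investigators, whether or not they need it. From then on, the adverse-event, withdrawal and outcome judgements those investigators make about that patient are unblinded, and judgements of similar events elsewhere may be coloured.

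The number affected is not given and is probably small. One patient is 0.6% of 180, and even an assumed 25-point distortion in that patient would move the group difference by 0.42 points against a 15-point target. Larger shifts need several SUSARs in one arm together with a large distortion, and nothing in the article supports either. The case for changing the text rests on an avoidable loss of blinding at very low cost, not on a demonstrated bias in the result.

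**What to change.** Replace the last sentence of Section 2.10.3 with wording to this effect: the independent person who performs the randomization breaks the code and sends the allocation directly to the ethics committee and the DSMB; investigators, CT readers and analysts remain blinded unless a need to know is documented; each disclosure is logged with its recipient, date and reason. The investigator would still report the event itself.

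In Section 2.7, name this as the one exception to the investigators' lack of access. Because that section also calls the person who randomizes an investigator, state there that the blinded group excludes that person.

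The cost is a few lines of text and one extra step in the reporting route. The independent randomizer, the ethics committee and the DSMB are already part of the plan, and sample size, treatment and analysis do not change.
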